## 2.4.5. Dependent and Independent Variables (Quantitative)

### 2.4.5.1. Dependent Variables (Outcome Measures for Summative Evaluation)

**Overtreatment and undertreatment.** Using the last A1c value in a time period we will define overtreatment if it is less than the thresholds of 6.5% (we will evaluate 6.0% and 7.0% for sensitivity analysis). If the same A1c value is greater than 9.0%, it is considered undertreatment. Those in the range of 6.5% to 9.0% are considered to be in moderate glycemic control and will be used as the reference group in statistical analyses.

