**Comorbidities.** Using ICD 9CM codes we will create indicators of advanced complications of diabetes, limited life expectancy, cardiovascular or ischemic vascular disease, and major medical and mental health conditions that would impact benefit or risk of tight control based upon previously published taxonomies.

**Demographic Variables.** We have developed algorithms to process multiple entries of patient data over time and from a variety of sources to optimize the demographic information available for research. Sources include many years of VA inpatient and outpatient data with multiple fields and Medicare data. Consequently, we have nearly complete and largely confirmed assignments for most variables, including age and sex. Because of limitations in data concerning race/ethnicity, we will not assess this variable.

**2.4.6. Identification of High and Low Performers.** High and low performers will be identified based on changes in facility overtreatment rates pre- and post-initiative (rather than on absolute values). Those with the greatest (high performers) and least reduction (low performers) in overtreatment rates will be selected. To

minimize issues related to regression to the mean, we will focus on facilities that were mid-performing at baseline (2nd and 3rd quartiles). See Fig. 4. Among the middle-performing facilities at baseline, we will select those facilities with the greatest reduction in overtreatment rates (high performers) and those with the least reduction (low performers). We will also select from among the highest performers at baseline who improved at all as well as some low performers at baseline who stayed low. It is impossible to know how many facilities will fall into these categories; but we are anticipating approximately 5-10 in each group (total n~30). Aim 3 does not include hypothesis testing, but is instead looking for identifying patterns of provider and facility characteristics associated with performance status (high vs. low). Our methods of analyses (matrix and qualitative comparative analysis) allow for a small sample size. Performance status will be determined independently of Choosing Wisely participation status; selected sites will likely include those facilities choosing the hypoglycemia initiative alone or both hypoglycemia and low back pain initiatives. If entire VISNs participate

[figure not shown]

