**Aim 1.** To assess the *overall* impact, both intended and unintended, of the Choosing Wisely Initiative. All analyses will be conducted for various subgroups of high risk patients. Due to the nature of the outcome variable in the quantitative aims (Aims 1 and 2), the primary statistical technique for these two aims will be logistic regression. The “logit” (i.e., log of odds) of the presence of an event is regressed on a list of independent variables. We will use odds ratios (=exponentiation of the estimated regression coefficients) and their confidence intervals for the hypothesis testing. An odds ratio larger (smaller) than 1 with a 95% confidence interval not containing 1 indicates a higher (lower) likelihood of the occurrence of an event for the group in comparison relative to the reference group in an independent variable. In Aim 1 we will use multinomial logistic regressions to model the outcome variable, a polytomous variable. In the models the polytomous variable is treated as a nominal variable and a value in the variable is treated as the reference group; separate logistic regression models for the probabilities of non-reference groups against the reference group are constructed and estimated simultaneously. This approach is more efficient than separately conducting two logistic regression models (i.e., the overtreated versus those in moderate control and the

undertreated versus those in moderate control). The primary exposure variable in both H1.1 and H1.2 is the group indicator variable. Along with the previously listed independent variables, a patient's glycemic control status in the pre-initiation period will also be included in the models as a control variable. We will assess both the implementation and sustainability phases of the initiative.

**Aim 2.** To assess the impact of facility commitment to quality, teaching intensity, and safety culture on patients' likelihood of overtreatment. We will use a similar modeling strategy to Aim1 for this aim but employ binary logistic regression models, because the hypotheses focus on overtreatment (a binary variable: overtreatment versus moderate control). We will construct separate models for each of H2.1a, H2.1b, and H2.1c. We will also evaluate the associations among the three primary exposures variables in the hypotheses, and construct a statistical model including all three variables and compare with the separate models.

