**2.5. Contingencies, Limitations, and Other Considerations.** There are several factors with significant potential impact on the project including timing and completeness of data. First, the initiative may be delayed (although according to the co-Chair, it is on schedule). Therefore, we have built in a one-year period for implementation which should accommodate a delay of up to six months. However, if necessary, we will request an extension of the project by the necessary amount of time. CMS data is likely to be delayed, but VA data alone should suffice for the key variables. As a natural experiment, we cannot predict with certainty how many facilities will choose to focus on hypoglycemic risk and sample size may be jeopardized if that number is insufficient. However, we are aware of three VISNs who have expressed interest in this project, especially because of its potential to reduce the costs associated with hypoglycemia in the elderly, e.g., hip fracture from falls. Second, the project is contingent upon obtaining data from busy providers. We are taking several approaches to this concern: (1) We have limited the surveys to a single one and minimized respondent burden as much as possible; (2) we have limited surveys to high/low performers allowing us to concentrate our recruitment efforts; (3) Office of Primary Care is strongly committed to this initiative and will promote participation in surveys; (4) PBM is strongly committed to working with clinical pharmacy specialists in the field; and (4) members of the research team, steering committee, and DM-QUERI have extensive social networks which will enable identification of individuals who can facilitate data collection. The study design is quasi-experimental using a natural experiment, so adopters and non-adopters may differ significantly at baseline. Our paired pre-post analysis for each facility based upon its implementation date will help to ameliorate this concern. We are studying a single disorder – diabetes - and findings may not generalize to other conditions. Nevertheless, DM is not only prevalent, but has been a good model for issues related to chronic disease. In addition, a key stakeholder group is not included in this proposal – patients with diabetes and their families. Anecdotally, it appears that some patients, who like clinicians, have been subjected to the marketing campaigns of the ADA, National Diabetes Education Project, and pharmaceutical companies, are reluctant to relax their levels of glycemic control. In addition, clinician-patient interactions affect the choice of targets. We omitted this important group for two reasons. First, the expanded scope of the project could not be

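### Aim 1 adjusts for baseline glycaemia only through a control status, apparently a three-level category from one A1c, so part of any baseline A1c difference between self-selected facilities remains as a spurious group effect

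*Protocol*

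**What the plan says.** **Baseline term.** Section 2.4.8, Aim 1, fits a multinomial logistic model to the post-initiative outcome, with the facility's participation group as exposure: "a patient's glycemic control status in the pre-initiation period will also be included in the models as a control variable".

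**Definition of status.** Section 2.4.8 does not define the status separately for the baseline period. The only classification in the protocol is that of the outcome, in 2.4.5.1: "Using the last A1c value in a time period we will define overtreatment if it is less than the thresholds of 6.5" percent. Values above 9.0% are undertreatment, and "Those in the range of 6.5% to 9.0% are considered to be in moderate glycemic control". For other cuts, "we will evaluate 6.0% and 7.0% for sensitivity analysis".

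**Other controls.** Section 2.4.5.2 lists comorbidity ("we will create indicators of advanced complications of diabetes, limited life expectancy, cardiovascular or ischemic vascular disease") and demographic variables ("we have nearly complete and largely confirmed assignments for most variables, including age and sex"). Section 2.4.8 enters the independent variables as controls and treats facility and VISN as random effects.

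**Exposure and data.** Section 2.4 states that exposure is not random and that causal inferences will be drawn cautiously. Section 2.5 grants that "adopters and non-adopters may differ significantly at baseline" and relies on a paired pre-post analysis per facility to ease this. Section 2.4.7 plans to extract laboratory A1c values from 2012 to 2016.

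**The concern.** H1.1 compares patients in facilities that chose the hypoglycaemia focus with patients elsewhere. If the groups start at different A1c levels, the baseline glycaemic covariate has to absorb that difference.

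A three-level category does this poorly. A patient at 6.5% and one at 9.0% before the initiative get the same covariate value, although their chances of a later value below 6.5% are very different. A single A1c is also a noisy measure of a patient's usual level. For both reasons, patients with equal status in two groups of facilities can still differ in true glycaemia, and the model attributes the rest to the group.

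The other planned elements do not close this gap. Random effects handle correlation within facilities and VISNs; they do not remove a mean difference between exposure groups. The 6.0% and 7.0% sensitivity thresholds are further cuts of the same single value. The paired pre-post analysis in 2.5 has no counterpart in the Aim 1 model of 2.4.8. At stake is whether a modest odds ratio for H1.1 reflects the initiative or the starting point.

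**Working it through.** **1. The effect to compare against (2.4.4).** The power section uses 0.290 against 0.273, with 130 facilities and 300 patients each.
- Odds ratio: (0.273/0.727)/(0.290/0.710) = 0.919; log-odds difference 0.084; inverted, 1.09.
- The stated power of more than 0.8 can be reproduced. Assume a 65:65 split and read the facility range 24.7% to 32.7% as a 95% range: between-facility variance = [(logit 0.327 − logit 0.247)/3.92]² = 0.010.
- Variance = [0.010 + 1/(300 × 0.290 × 0.710) + 0.010 + 1/(300 × 0.273 × 0.727)]/65 = (0.0262 + 0.0268)/65 = 0.000815, so the SE is 0.0285.
- Power = Φ(0.0841/0.0285 − 1.96) = 0.84.

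**2. Set-up of the no-effect simulation.** Patients are simulated in two groups with no initiative effect. Later overtreatment against moderate control is regressed on group with different baseline adjustments. From the protocol: about 28.6% below 6.5%, and about half below 7%. Assumed, because the protocol gives neither: the baseline gap between groups, and a correlation of 0.5, 0.65 or 0.8 between single A1c values a year apart. Two mechanisms are tried:
- *Measured:* the gap acts on the later value only through the measured baseline A1c.
- *Persistent:* the groups differ in patients' underlying level, and each A1c is a noisy reading of it.

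**3. Results with one group 0.1 A1c point lower at baseline** (about 28.5% against 32.4% overtreated; 400,000 patients; SE about 0.007 on the log odds ratio). A value of 1.00 would be correct.

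| Mechanism | Correlation | Unadjusted | Three-level status | One continuous A1c |
|---|---|---|---|---|
| Measured | 0.5 | 1.081 | 1.018 | 0.989 |
| Measured | 0.65 | 1.118 | 1.037 | 1.000 |
| Measured | 0.8 | 1.143 | 1.058 | 1.004 |
| Persistent | 0.5 | 1.180 | 1.128 | 1.101 |
| Persistent | 0.65 | 1.183 | 1.116 | 1.084 |
| Persistent | 0.8 | 1.189 | 1.117 | 1.069 |

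With the sign reversed (0.1 point higher), status adjustment gives 0.96 to 0.98 (measured) and 0.88 to 0.89 (persistent). Over all gaps tried (−0.1 to +0.2 point), the status leaves about 20 to 45% of the unadjusted log odds ratio under the measured mechanism and about 50 to 77% under the persistent one.

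**4. A second set-up, including repeated values.** A shifted lognormal was fitted to 10%, 28.6% and 49% below 6.0, 6.5 and 7.0%. A persistent shift of 0.1 SD gives 28.6% against 32.1%, a 3.5-point gap. At correlations 0.5, 0.65 and 0.8:
- three-level status: 1.117, 1.101, 1.099
- one continuous A1c: 1.098, 1.077, 1.064
- continuous mean of three prior values: 1.057, 1.040, 1.031

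On the log scale, one continuous value cuts the bias by 16 to 34%. For example, 1 − ln 1.098/ln 1.117 = 0.16. The mean of three cuts it by 50 to 67%. Repeating the 3.5-point gap under the measured mechanism gives about 1.03 to 1.04 with the status and about 1.00 with continuous A1c.

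**The case against.** **The coding is inferred.** The protocol never says that the baseline status uses the outcome's cut-points, and covariate coding is often left to an SAP. This stands as a limit on certainty. But the protocol itself names the covariate as a status, and it contains only one classification of glycaemic control.

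**Other controls exist.** A reader might infer that the status is the only patient-level baseline control. It is not: comorbidity indicators, age and sex are also in the model. It is the only glycaemic one.

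**The assumed gap is large.** The 3.5 points lie within the ranges for single facilities, but the contrast is between group averages. Section 2.4.2 expects at least 4 to 6 VISNs of about 5 facilities, so 20 to 30. Reading 24.7% to 32.7% as ±2 SD gives an SD of 2.0 points. If choice were unrelated to the rate, 25 against 105 facilities would differ with SE 2.0 × √(1/25 + 1/105) = 0.45 points. The wider range in the background (20.4% to 45.9%, SD 6.4) gives 1.4. This stands: chance alone would rarely give 3.5 points under the narrow range. It ignores self-selection and choice at VISN level, either of which could widen the gap.

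**Crossing the threshold by noise is not bias.** A reader might point to a patient moving from 6.4% to 6.6% as evidence against the analysis. Such movement occurs in both groups and creates no group effect without a baseline difference, so it plays no part here.

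**The shared cut-point is only part of the cause.** Under the persistent mechanism much of the residual comes from using one noisy value. This stands, and it is why averaging several values matters.

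**Conclusion.** The point holds in a limited form. On the protocol's only definition, Aim 1 adjusts for baseline glycaemia with a coarse category from a single A1c. In a comparison of self-selected facilities, that leaves part of any baseline difference in the group effect. Flexible continuous adjustment came closer to no effect under both mechanisms, and the data are already in the planned extract.

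The size is conditional. With a 3.5-point gap and correlation 0.5 to 0.8, the bias is small if the gap acts only through measured A1c. Only if the gap is persistent does it become comparable to the planned detectable effect. The protocol gives no baseline gap between groups, no correlation and no mechanism, so it does not support a flat statement that the bias equals the planned effect.

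Nor do the documents support the stronger reading that baseline differences pass through whole, or that they would produce a false benefit. The leakage is partial and its sign is unknown: adopters starting with higher A1c would appear to benefit, and adopters starting lower could have a real benefit masked. This should be changed, but it does not invalidate the design.

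**What to change.** In section 2.4.8, Aim 1, replace the glycaemic control status by wording such as: the models will adjust for the patient's pre-initiative A1c, taken as the mean of the available values in the 12 to 24 months before 4/1/2014 and entered as a restricted cubic spline; patients with no prior value will be kept with a missing-baseline indicator; the three-level status will be used in a sensitivity analysis.

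The indicator is needed because the cohort is dynamic (2.4.6) and entry requires only one A1c (2.4.3). Section 2.4.8 already allows an unknown subcategory as an alternative to complete cases. The number with no prior value should be reported by group, since those patients get no glycaemic adjustment.

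Do not require the same covariate in Aim 2. Quality commitment, teaching intensity and safety culture are standing facility traits that may already have shaped baseline A1c, so adjusting for it could remove the association being tested.

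The cost is a sentence or two, a few more model parameters, a coefficient that is harder to present than a category, and the handling of missing baselines. No new data are needed. The change reduces the bias but does not remove all of it under a persistent difference. Carrying the pre-post comparison promised in section 2.5 into the Aim 1 analysis would be a useful complement.

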#### **2.4.9. Qualitative Analyses**

**Aim 3.** To identify configurations of the implementation strategy (Choosing Wisely toolkit), provider characteristics, and organizational level factors that are associated with successful reduction of overtreatment rates by comparing high and low performers. Data collection and analysis for these research questions will use a mixed methods approach, as described below.

***Provider/Clinician/Clinical Manager Surveys.*** Provider surveys (see Appendix) will be administered approximately 1 year following implementation of the initiative to clinical leaders and PCPs and other clinicians at the low and high-performing sites. Survey domains are derived from our conceptual framework. The surveys will obtain data on provider and organizational factors potentially affecting overtreatment rates. Provider characteristics include clinician type (MD, DO, NP, PA, CPS), years in practice, and gender. The survey is based on the Diabetes Attitudes Survey and the Veterans Assessment and Improvement Laboratory (VAIL) VISN 22 Survey of Primary Care Team Experiences. We will also assess clinicians' knowledge and attitudes towards glycemic targets. We will assess efficacy using the Provider Abilities subscale from the Midwest Clinicians' Network Barriers to Diabetes Care Survey questionnaire, adding items modeled after Glazier et al. and questions about factors such as competing priorities. We will use the Consolidated Framework for Implementation Research (CFIR) framework to define potentially influential organizational factors. The survey will consist of questions assessing the potential importance of each CFIR construct in implementing the Choosing Wisely Initiative. This survey has been used in the evaluation of four initiatives (E-Consults, SCAN-ECHO, Specialty Care Neighborhood, and Mini-Residencies) so far in the Specialty Care Evaluation project. We will survey up to 30 individuals in each of the ~30 identified low and high performing sites (~900 surveys). We will conduct the survey online (Inquisit® software) with follow up emails, letters, and phone calls as needed. Respondent burden will not exceed 25 minutes. Respondents will be given the opportunity to enter into a lottery for an iPad or Android Tablet.

***Semi-Structured Interviews.*** A semi-structured interview guide will be developed consisting of questions designed to obtain input on the organizational and provider factors identified as most important from the surveys. As part of the Specialty Care Evaluation project, we have developed multiple interview guides addressing most of the CFIR constructs. These questions have been used successfully thus far for four different Specialty Care initiatives; for a draft, we have selected potentially relevant questions from these previously developed guides and tailored them for this study (see Appendix). The interviews will also contain questions about which elements of the toolkit have been implemented. Potential respondents (the clinical pharmacy specialist, director of primary care, and primary care providers) will be contacted via an email invitation followed by a phone call. All interviews will be conducted by two research team members, with one conducting the interview (audio-taped) and one taking field notes. Based on our experience with the Evaluation Center and others, we will conduct approximately 5 interviews per facility for the highest and lowest performers (n=150). If saturation is not achieved, we will conduct additional interviews.

***Site Visits.*** Once the analyses have been completed and the key constructs identified (see analysis plan below), we will conduct site visits to the highest performing sites; we will select facilities of various levels of complexity and location. (We have budgeted for 8 visits.) The primary purpose of the site visits will be to obtain detailed information on site-level manifestation of the constructs associated with implementation success. Interviews will be conducted with the clinical pharmacy specialists, primary care providers, and clinical managers. Clinics will be visited and artifacts collected, e.g., education materials, screen shots of CPRS (using test patients) illustrating decision support, clinical reminders, and lab comments on A1c. Site visits will require 2 days by a 2-person team. We will use methods adapted from prior work conducted by colleagues with the Center for Organization, Leadership, and Management Research (COLMR).

**2.4.10. Mixed Methods Analysis.** The unit of analysis for our mixed methods approach will be the medical center. Our sample size of low and high performing sites will make it impossible to conduct formal tests of hypotheses, but we can still analyze the data to obtain important information on those provider and organizational factors potentially associated with performance. The Diabetes QUERI is collecting these data across studies for a VA QUERI database of implementation findings, which will eventually allow us to perform hypothesis testing using a meta-analytic approach. As we have done in multiple studies of national implementation efforts, our analysis will be sufficient for providing useful feedback to our operational partners regarding those provider and organizational factors needing attention for improving dissemination.

Our initial analyses will focus on identifying those factors from the *provider surveys* that at least 75% of respondents identified as important or very important for affecting successful implementation of the Choosing Wisely Initiative. In our previous work with the Specialty Care Evaluation project, this percentage allows us to identify 10-12 key organizational factors on which we can focus our interview questions. We will also look at correlations between provider characteristics and performance status (low vs. high).

To analyze the *interview* data, our focus will be on coding the data according to components of the Choosing Wisely toolkit and constructs from the CFIR. Most of the interview guide questions will define specific toolkit components and CFIR constructs that will allow the researchers to efficiently collect and evaluate the appropriate data. Following each interview, two members of our research team will review interview notes. Each member of the team independently assigns the appropriate CFIR code(s) to each response. The team then seeks consensus on the codes for all responses for a given interview. Each team member then independently reviews the responses associated with each construct and assigns a 0 or 1 rating to the construct, which reflects the respondent’s perception of the manifestation of the construct in the organization (0 = negative, 1 = positive). Choosing Wisely toolkit components will be assigned either a zero (absent) or 1 (present). Once this process is completed for all respondents at a given site, the team meets to assign an overall rating for each construct at the site level, considering the ratings across respondents and each respondent’s role in and knowledge of the Choosing Wisely Initiative. The findings will be entered into a matrix, with sites as columns, constructs/ components as rows, and ratings (0 or 1) as the cell entries. Data will be analyzed initially using a matrix analysis approach to examine potential correlations of the ratings with performance (i.e., ratings of 1 with high performance and ratings of 0 with low performance).

The matrix will also be analyzed using qualitative comparative analysis (QCA), which is a case-oriented,

[figure not shown]

comparative analytic method based on set-theoretic relationships (as opposed to statistical or correlational relationships) between explanatory factors and an outcome. This approach allows for systematic cross-case comparisons across a small to intermediate number of cases, which is the situation for this study. It is useful for studying causal complexity—when different combinations of factors can lead to the same outcome, when some

factors may only be causal in the presence of other factors, and when the absence of the outcome has a different causal pathway than simply the absence of factors associated with the outcome (i.e., causal asymmetry). We will define approximately six to eight independent variables for use in the QCA. Selection of these variables will be based on the findings from the matrix analysis and will include those toolkit components and those CFIR constructs

that (1) distinguish between low and high performers (i.e., negative or absent in low sites, positive or present in high sites); (2) were absent or negative in most sites, regardless of performance; and (3) were positive or present in most sites, regardless of performance.

QCA will allow us to determine those constructs whose positive manifestations (rating of 1) are *necessary* for achieving high performance. A construct is considered necessary if it is always positive in high-performing sites. That is, high performance cannot occur in the absence of a positive manifestation of the construct, but its presence does not guarantee high performance. QCA will also determine those constructs or combination of constructs that are *sufficient* for achieving high performance. A construct or combination of constructs is sufficient for high performance if high performance always occurs when the positive manifestation of the construct or combination of positive constructs is present. The presence of a sufficient construct or combination of constructs guarantees high performance when the necessary constructs are present. For example, we may find that a particular toolkit component is necessary, but not sufficient for high performance. Thus, a policy recommendation might be to recommend that all facilities at a minimum implement the necessary component, as without it facilities have no chance of success. We may also find that no components are necessary, but three of the available components are sufficient. Thus, a policy recommendation might be to recommend at least one of the three components, and allow facilities to select from among any of the three sufficient components. For example, among the components likely to be necessary, if not sufficient, are clinical reminders and local audit and feedback.

In addition to conducting analyses of necessity and sufficiency for the outcome of being a high performer, we will conduct similar analyses with the outcome of being a low performing facility. This is required because the causal recipe to failure can be as useful within a learning organization as that of success. [name] will provide expert consultation on the use of QCA. She has used this approach previously in determining best practices in VHA's MOVE! Weight Management Program for Veterans and is PI on a current Agency for Healthcare Research and Quality-funded methods grant to assess the feasibility of using QCA to explain heterogeneity within systematic reviews of complex interventions. Once the important constructs and combinations of constructs have been identified from our analyses, we will go back to the summary memos from our interviews to obtain additional information on the specific practices at sites in which these constructs were positively manifested. In addition, data from the visits to high performing sites will be analyzed descriptively for identifying best practices, and the findings from these analyses will then become the basis of our specific recommendations for improving dissemination of the Choosing Wisely Initiative.

**2.5. Contingencies, Limitations, and Other Considerations.** There are several factors with significant potential impact on the project including timing and completeness of data. First, the initiative may be delayed (although according to the co-Chair, it is on schedule). Therefore, we have built in a one-year period for implementation which should accommodate a delay of up to six months. However, if necessary, we will request an extension of the project by the necessary amount of time. CMS data is likely to be delayed, but VA data alone should suffice for the key variables. As a natural experiment, we cannot predict with certainty how many facilities will choose to focus on hypoglycemic risk and sample size may be jeopardized if that number is insufficient. However, we are aware of three VISNs who have expressed interest in this project, especially because of its potential to reduce the costs associated with hypoglycemia in the elderly, e.g., hip fracture from falls. Second, the project is contingent upon obtaining data from busy providers. We are taking several approaches to this concern: (1) We have limited the surveys to a single one and minimized respondent burden as much as possible; (2) we have limited surveys to high/low performers allowing us to concentrate our recruitment efforts; (3) Office of Primary Care is strongly committed to this initiative and will promote participation in surveys; (4) PBM is strongly committed to working with clinical pharmacy specialists in the field; and (4) members of the research team, steering committee, and DM-QUERI have extensive social networks which will enable identification of individuals who can facilitate data collection. The study design is quasi-experimental using a natural experiment, so adopters and non-adopters may differ significantly at baseline. Our paired pre-post analysis for each facility based upon its implementation date will help to ameliorate this concern. We are studying a single disorder – diabetes - and findings may not generalize to other conditions. Nevertheless, DM is not only prevalent, but has been a good model for issues related to chronic disease. In addition, a key stakeholder group is not included in this proposal – patients with diabetes and their families. Anecdotally, it appears that some patients, who like clinicians, have been subjected to the marketing campaigns of the ADA, National Diabetes Education Project, and pharmaceutical companies, are reluctant to relax their levels of glycemic control. In addition, clinician-patient interactions affect the choice of targets. We omitted this important group for two reasons. First, the expanded scope of the project could not be

accomplished within budget. Second, evaluation of patient factors would be complicated by the fact that many patients at higher risk for hypoglycemic events may comprise a vulnerable population by virtue of age, cognitive impairment, and alcohol/substance use and/or serious mental conditions, which might compromise decision-making, and necessitate inclusion of family members. Therefore, we plan to submit a pilot proposal (RRP) specifically addressing patients and clinician-patient interactions. For Aim 3, the number of facilities is too large for intensive case studies of all of them, but too small for a regression approach. QCA addresses the middle ground and does so effectively. In addition, our choice of QCA was based on the fact that VHA's Choosing Wisely initiative is a complex intervention nested within a complex and open health care system, and as such issues of causal attribution are more problematic. In addition, some components may only be causal when present in association with other components (conjunctural causality). Similar outcomes may result from different causal pathways (equi-finality). Finally, we recognize that the Choosing Wisely initiative is occurring in a changing health care environment where something completely unexpected is likely to happen. We will be attentive to developments that potentially affect the initiative and be prepared to modify our procedures to take them into account. For example, addition of components to the toolkit or national adoption of a performance measure or inclusion of a monitor in the PCP/PCMH dashboard during the period of implementation would necessitate modification of the surveys and interview guides. The timing would dictate whether or not modification of the time points for analyses is necessary.

**3.0. Dissemination of Findings and Project Management.** The dissemination plan is illustrated in Table 1 . In addition to presentations at national meetings (e.g., VA HSR&D Service meetings, Academy Health) and

submission of results to peer-reviewed journals, there are other means for dissemination of the findings. The PI serves on committees in VISN10, including the Chronic Care and Health Systems Design Committees. Results, particularly those with policy implications, will be shared with these committees along with the Executive Leadership Council (which includes all the Service Line Directors and Chiefs of Staff), the Network Chief

| Table 1. End Users                                                                                          | Needs                                | Means                                                                                                                                                                    |
|--------------------------------------------------------------------------------------------------------------------|---------------------------------------------|---------------------------------------------------------------------------------------------------------------------------------------------------------------------------------|
| Researchers                                                                                                        | Scientific findings                         | Publications, scientific meetings                                                                                                                                               |
| Clinical Operations - Service/Section Chiefs                                                                       | Scientific and Operations-relevant findings | Presentations at Field Advisory Committee Meetings by PI (FAC member) and [name] (FAC chair)                                                                                 |
| Managers - CMOs, QMOs, VISN Directors and facility equivalents                                                     | Operations-relevant findings                | Executive briefs presented by [name], CMO, VISN10 to CMOs and by [name], Director, VISN12 to other VISN directors and National Leadership Board.                      |
| Policy – Offices of Primary Care, Specialty Care, PBM, Academic Affiliations                                       | Operations-relevant findings                | Executive briefs will be presented by representatives of these offices serving on the Steering Committee                                                                        |
| Choosing Wisely Initiative/ Interagency Task Force                                                                 | Operations-relevant findings                | Executive briefs will be presented by representatives of these offices serving on the Steering Committee                                                                        |
